### Data analysis

Usual descriptive statistics will be used to summarize the results. Means per group, mean differences between the groups, rates, and rate differences will be analyzed with 95 % confidence intervals. Multivariate analyses with linear and logistic regressions will be performed in order to explore the practice effect and further potential covariates and cofactors. The design effect of clustering (and intra-cluster correlation) will be calculated to aid sample size estimation for a future cluster-randomized trial.

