### Target group and sample size

The target group will consist of overweight (BMI ≥25 kg/m^2^) [19] and/or inactive patients (<1 h exercise/week) visiting GPs for routine health checks (Check-Up 35 (age ≥35 years) and/or GOÄ29 (age ≥18 years)).

The primary outcome is the increase in steps/day after 6 months. In the intervention group (IG), an additional mean increase of 1000 steps/day in contrast to the controls is a feasible difference with a risk reduction in metabolic syndrome, BMI, fat mass, etc. [8]. It is expected that in the treatment group there is a larger mean increase of 1000 steps/day with a standard deviation of 2200 steps as a conservative estimation. Then, a sample size of 105 patients per group would be required in order to detect a difference between groups at a significance level of 0.05 (two-tailed) with a power of 0.90. Considering an attrition rate of approximately 30 % over the course of the study, a total of 300 subjects (150 for each group) will be enrolled. The intra-cluster correlation (ICC) is expected to be small but is unknown, and consequently, the power of this study may be reduced. Success rates like the rate of patients reaching an increase of more than 1000 steps or reaching the target of 10,000 can be estimated with 95 % confidence intervals reduced than ±10 %.

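### The planned 95% confidence intervals for the group comparison make no stated allowance for patients being nested in practices, so for any positive ICC they would be too narrow

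*Protocol article*

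**What the plan says.** All places are in the protocol article.

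- **Design and Recruitment.** Allocation is by city. Up to 20 practices per region take part, with 8 to 10 patients each and 300 in total. GPs and nurses are trained, and they deliver the intervention or the control advice.
- **Target group and sample size.** The comparison is "an additional mean increase of 1000 steps/day in contrast to the controls", with "a standard deviation of 2200 steps as a conservative estimation", "at a significance level of 0.05 (two-tailed) with a power of 0.90". From this, "a sample size of 105 patients per group would be required", raised to 150 per group for about 30% attrition. On clustering: "The intra-cluster correlation (ICC) is expected to be small but is unknown". The only consequence drawn is that power may be lower. The section then says success rates can be estimated to within ±10%.
- **Data analysis.** "Means per group, mean differences between the groups, rates, and rate differences will be analyzed with" 95% confidence intervals. Practice appears next: "linear and logistic regressions will be performed in order to explore the practice effect", together with other covariates. The design effect and ICC are to be calculated, and the stated purpose is the sample size of a future cluster-randomized trial.

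The article names no mixed model, GEE, cluster-robust variance or practice-level analysis for the group comparison.

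**The concern.** Patients of one practice share the same GP, nurses, training session and neighbourhood, so their step changes may be correlated. The article accepts this by discussing an ICC. When whole practices belong to one arm, positive correlation inflates the variance of the difference between arms. An interval computed as if patients were independent is then too short.

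The protocol plans to compute the quantity that would correct this, but assigns it to another study. Its one caveat concerns power. Loss of power is what clustering costs when the analysis allows for it. When the analysis does not, coverage also falls and the false-positive rate rises, and the article does not mention this. The step difference is the primary patient-level comparison, and the Discussion intends the effect estimates to inform a later trial, so overstated precision would be carried forward.

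**Working it through.** **Inputs from the article:** difference 1000 steps/day; SD 2200; two-sided alpha 0.05; power 0.90; 105 evaluable per group; 30% attrition; at most 20 practices per arm.

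**Assumed:** ICC 0.01, 0.05 and 0.10 (none is given); equal practice sizes; 20 or 15 practices per arm. Twenty is the stated ceiling. Fifteen is what 150 enrolled patients at 10 per practice would need (150/10 = 15).

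**1. The plan's own figures.** For independent patients, n per group = 2 × (1.960 + 1.282)² × 2200² / 1000² = 101.7, so 102; the t-test version gives 103. The stated 105 is within 3% of this. Then 105/0.70 = 150 per group, 300 in total. The size therefore reproduces with a design effect of 1 and leaves almost no room for a larger one (105/102 = 1.03).

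**2. The ±10% statement.** At n = 105 and a rate of 50%, the unadjusted half-width is 1.96 × √(0.25/105) = 9.6 points. It passes 10 points once the design effect exceeds (10/9.56)² ≈ 1.09. At 5.25 completers per practice that is an ICC of about 0.09/4.25 ≈ 0.022. The statement thus matches an unadjusted calculation.

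**3. Unadjusted interval for the step difference.** SE = 2200 × √(2/105) = 303.6. Half-width = 1.96 × 303.6 = 595 steps/day.

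**4. With clustering.** Design effect DE = 1 + (m − 1) × ICC, where m is completers per practice. The correct half-width is 595 × √DE. True coverage of the unadjusted interval is 2Φ(1.96/√DE) − 1, and its false-positive rate is 1 minus that. All figures use the normal approximation, so only the design effect changes between rows.

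| Practices per arm | m | ICC | DE | Half-width needed | Coverage of unadjusted 95% CI | False-positive rate |
|---|---|---|---|---|---|---|
| 20 | 5.25 | 0.01 | 1.04 | 608 | 94.5% | 5.5% |
| 20 | 5.25 | 0.05 | 1.21 | 655 | 92.5% | 7.5% |
| 20 | 5.25 | 0.10 | 1.43 | 710 | 89.9% | 10.1% |
| 15 | 7 | 0.05 | 1.30 | 679 | 91.4% | 8.6% |
| 15 | 7 | 0.10 | 1.60 | 753 | 87.9% | 12.1% |

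With 20 practices per arm the interval should be 2%, 10% and 19% wider at the three ICC values. Small-sample degrees of freedom would add a little more: t on 38 df is 2.024 against 1.960, a factor of 1.033.

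**5. Practice as a fixed factor.** Each practice belongs to one arm. An intercept, a group indicator and 39 dummies for 40 practices make 41 columns, but the rank is 40. In that specification the group effect cannot be estimated. With practice as a random effect or as the cluster unit in GEE, this does not arise.

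**The case against.** **The article does not name a variance estimator.** It is a condensed document, and the estimator behind an interval is commonly left to an analysis plan. That is fair as far as it goes, and silence alone would not be a finding. But the article goes beyond silence: it gives the design effect and ICC a purpose, and that purpose is another trial. The sample size also fits independent patients. Unadjusted intervals are the supported reading, though still an inference. The ±10% statement is weaker evidence, because at 150 per group or at rates far from 50% it could hold under moderate clustering too.

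**Clustering is acknowledged.** It is: the ICC is called unknown, the practice effect will be explored, and the design effect will be calculated. A careful reader could widen the intervals afterwards. The reported intervals would still be too short, and the caveat covers power only.

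**The size depends on an assumed ICC.** This stands. The article expects a small value, and at 0.01 the loss of coverage is about half a percentage point.

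**This is a non-randomized feasibility study.** True, and adjustment for practice does not separate group from city. But the article fixes a two-sided 0.05 comparison at 90% power, so the intervals should have the coverage they claim.

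**A stronger reading.** A reader might infer that the planned regressions cannot return a group effect at all, and that the logistic model for the 10,000-step target will fail through separation. The article does not support this. It does not say that practice enters as fixed dummies beside group, nor that those exploratory models supply the group effect. Both problems are conditional on that specification.

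**Conclusion.** The point holds in this form: between-group mean and rate differences are to be reported with 95% intervals for which no allowance for practice is stated, while the quantities that would correct them are reserved for a future trial. The direction is certain for any positive ICC, provided the intervals are computed without adjustment, which is what the text supports.

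The size is uncertain because the article gives no ICC. Over 0.01 to 0.10, with 105 completers per arm in 20 equal practices, true coverage runs from about 94.5% down to 89.9%. Fewer practices make it worse, to about 87.9% at ICC 0.10 with 15 per arm. The error is minor at the low end and material from about 0.05 upward.

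**What to change.** In the Data analysis section, state that between-group differences in means and rates, and their 95% confidence intervals, account for practice. Any of these would serve:

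- a mixed model with group as fixed effect, a random practice intercept and small-sample degrees of freedom;
- GEE clustered by practice with small-sample-corrected robust standard errors, which also suits the rates;
- an analysis of practice-level means.

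Report the ICC from this analysis, which also serves the planning purpose already stated. If practice is explored in the regressions, say that it enters as a random effect or cluster unit. As a fixed factor beside group it would be aliased with group, and it could cause separation in the logistic model. In the sample size section, extend the caveat to say that the ±10% precision also assumes independent patients.

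The cost is a change of wording and somewhat wider intervals, with no additional data. The change does not remove the confounding of group with city, which should remain a stated limitation.

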**Methods/design:**

The quasi-experimental, multi-center prospective feasibility study is designed for general practices in Cologne (intervention group) and Düsseldorf (control group), up to 20 per region. Eight to 10 inactive and/or overweight patients per practice will be recruited for a total of 300. General practitioners and at least one of their nurses for the intervention group will be trained in motivational interviewing and familiarized with low-threshold recommendations for exercise (activities of daily life (ADL), target of 10,000 steps/day) and additional tools (pedometers, activity diaries). Participants in the control group will only receive general advice (150 min of exercise/week). The primary aims are to evaluate the feasibility of this intervention and to determine whether it is possible to reach a mean increase of 1000 steps/day in the target group within 6 months. Secondary objectives focus on the number of patients who reach a target of 10,000 steps/day and their improvements in quality of life and decrease in body mass index, waist circumference, and blood pressure.

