## Methods/design

### Design

The 10,000 step study is a quasi-experimental, multi-centric prospective feasibility study. A quasi-experimental design is chosen because it is not possible to randomize the intervention according to individual patient or practitioners within the services at this moment. Ethical approval for the study was obtained from the ethics commission of the German Sport University Cologne (No. 18/2013). This protocol complies with the SPIRIT guideline of writing protocols.

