### Recruitment

A total of 714 GPs in Cologne will be informed by the Northrhine Medical Association and invited to take part in the study. The first 20 practices will be recruited into the study and trained to provide brief interventions. Likewise, a control group (CG) will be selected at a different location (Düsseldorf; in total 426 GPs) to prevent regional overlaps, mixing of study participants and participating physicians talking to each other. Düsseldorf has been selected because of its similarity and comparability in terms of size, region, and practitioners’ clientele.

Data for all patients registered for health checks (Check-Up 35/GOÄ29; anthropometric data, BMI, waist circumference, and blood pressure) will be documented. Patients who meet the inclusion criteria will be invited to participate in the study until the planned number of 8 to 10 participants per GP is achieved. Then, anthropometric data, arterial blood pressure (after 5 min of sitting) and questionnaires regarding sociodemographic factors including personal and family history will be collected at baseline (T1). Furthermore, individual lifestyle factors and SF-36 [20] health surveys will be collected both at baseline (T1) and as a follow-up 6 months later (T2). Within the intervention group, the brief intervention will be performed. The controls receive “usual care” only, i.e., general information given verbally about the goal of exercising 150 min/week. In case of non-participation, both the patients’ data and their reasons for non-participation will be documented providing their consent in written form (Fig. 1).

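### In a non-randomised comparison of one city with another, the planned group difference carries no adjustment and baseline covariates are only explored

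*Protocol article*

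**What the plan says.** All references are to the protocol article.

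- **Design:** "A quasi-experimental design is chosen because it is not possible to randomize the intervention according to individual patient or practitioners".
- **Abstract, Methods/design:** the setting is "general practices in Cologne (intervention group) and Düsseldorf (control group), up to 20 per region", so each group is one city.
- **Recruitment:** GPs in Cologne are invited, and "The first 20 practices will be recruited into the study and trained to provide brief interventions". The choice of control city is justified thus: "Düsseldorf has been selected because of its similarity and comparability in terms of size, region, and practitioners’ clientele". No matching of practices or patients is described.
- **Target group and sample size:** the primary outcome is the increase in steps/day at 6 months. It is sized as a two-sided comparison of two groups: difference 1000 steps/day, SD 2200, 90% power, 105 per group, and 150 per group after 30% attrition.
- **Data analysis:** group means, rates and their differences are reported with 95% confidence intervals, with no adjustment named. The section continues: "Multivariate analyses with linear and logistic regressions will be performed in order to explore the practice effect and further potential covariates and cofactors". The intra-cluster correlation is to be calculated for use in a later trial.
- **Discussion:** the effect sizes, the design effect and the explored prognostic factors are to feed the planning of a cluster-randomised trial. Sociodemographic factors of patients and GPs are said to be considered because they strongly affect lifestyle.

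**The concern.** Nothing in the design balances the two groups. Group follows from city, from which practices come forward, and from which patients those practices invite. Practices are trained according to their group, and nothing described hides the group from staff when they invite patients.

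In such a design, adjustment for baseline variables is the only analytic protection against measured confounding. The article gives that protection an exploratory role. The reported interval would then reflect sampling error but not differences in who was recruited. With the covariate set left open, the adjusted result could also be chosen after the data are seen. Since the effect size is to be carried into the planning of a larger trial, a distorted estimate would be carried forward with it.

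**Working it through.** **1. The plan's own figure.** Inputs from Target group and sample size: difference 1000, SD 2200, two-sided alpha 0.05, power 0.90.

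n per group = 2 × (1.960 + 1.282)² × 2200² / 1000² = 102 (103 with the t distribution). The stated 105 is close to this and gives power 0.909. Then 105 / 0.70 = 150 per group, 300 in total. The arithmetic is sound. The formula is that of an unadjusted difference between two independent means, which matches the Data analysis section.

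**2. Precision of the crude difference.** SE = 2200 × √(2/105) = 304 steps/day, so the 95% half-width is 1.96 × 304 ≈ 595. This ignores clustering by practice; a positive intra-cluster correlation would make the true SE larger.

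**3. What an assumed bias b would do.** With no true effect, the false-positive rate is P(|Z + b/304| > 1.96), and interval coverage is one minus that rate. The values of b are assumptions.

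| b, steps/day | False-positive rate | Coverage of 95% interval |
|---|---|---|
| 100 | 6.3% | 93.7% |
| 200 | 10.1% | 89.9% |
| 300 | 16.7% | 83.3% |
| 500 | 37.7% | 62.3% |

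A bias of 300 is about one SE and 30% of the target difference (300/1000). These rates refer to total bias from any source. They do not show what adjustment would correct.

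**4. What adjustment can and cannot reach.** Every intervention patient is in Cologne and every control patient in Düsseldorf. A city indicator would therefore be identical to the group indicator, and no regression can separate the two. Patient-level covariates can remove only differences in measured patient mix.

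**5. Baseline steps need care.** Let r be the correlation between baseline and follow-up steps (not given; 0.5 to 0.8 assumed), and suppose the groups differ at baseline by 500 steps/day.
- If both groups would regress to a common level, the change-score comparison is biased by (1 − r) × 500, which is 250 steps at r = 0.5 and 100 at r = 0.8. Baseline adjustment removes this.
- If instead the 500-step gap is stable, the change score is unbiased. The baseline-adjusted difference is then off by 500 − r × 500, again 250 to 100 steps.

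The documents cannot say which case applies, so neither analysis is safe on its own.

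**6. Cost in sample size.** If 2200 is the SD of change, the residual SD after baseline adjustment is 2200 × √((1 + r)/2). The formula in step 1 then gives 77 per group at r = 0.5 and 92 at r = 0.8. Before any allowance for clustering, baseline adjustment would need no more than the planned 105.

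**The case against.** The strongest reply is that this is a feasibility study that openly calls itself quasi-experimental, and that regressions with covariates are planned. A condensed article may leave the covariate list to a fuller document, and exploring covariates suits the aim of planning a later trial. Much of this stands, and it lowers the urgency. It does not dispose of the point, because the article itself sizes a between-group comparison at 90% power and itself gives covariates an exploratory role.

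A reader might infer more than the documents support:

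- **That the crude difference is declared the primary analysis.** The Data analysis section labels no analysis as primary, and the Abstract and Background also word the aim as a mean increase in the target group. The between-group reading rests on the sample-size section.
- **That all confounding passes into the estimate.** The outcome is a change, so stable differences in activity level between the cities largely cancel. What remains is whatever affects change: patient selection, practice volunteering, regression to the mean, and season if recruitment calendars differ, which nothing indicates.
- **That the GP counts (714 and 426) refute the claimed similarity of the cities.** They count doctors, not patients, and say nothing about case mix. The claim also covers practitioners' clientele, not just size.
- **That every useful covariate is already in hand.** Education and visit date are not named as collected items. It is also not stated that intervention patients' baseline steps precede counselling.

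**Conclusion.** The point holds in a limited form. As written, measured differences in patient mix that affect the 6-month change in steps are not removed from the between-group estimate. That estimate is the one the study is sized on and the one to be used for planning. Making a prespecified adjusted estimate the main one is a clear and cheap improvement over the stated method.

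The size of the problem is unknown. The rates of 10%, 17% and 38% rest on assumed biases of 200, 300 and 500 steps/day, an SD of 2200, 105 patients analysed per group, and no clustering. They show how sensitive a crude interval is to bias. They must not be read as the gain from adjustment, since any city effect would remain. Given the feasibility purpose, the change should be made but is not critical.

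**What to change.** 1. Name an adjusted between-group difference as the main between-group estimate, for mean change and for the rates, with practice accounted for as the cluster. Report the crude difference beside it.
2. Fix a short covariate set before the data are seen, from what the article says is collected at T1: age, sex and other sociodemographic items from the questionnaire, BMI, and activity from the modified IPAQ. The article does not itemise the sociodemographic questionnaire, so confirm that each item is there.
3. Add baseline steps only if they are confirmed to be measured before counselling in the intervention group. If so, report both the change-score and the baseline-adjusted result, because they rest on different assumptions in non-equivalent groups. Add education and calendar month only if they are recorded.
4. Keep any further covariates exploratory and label them so.
5. State in the analysis and the conclusions that city and intervention are fully aliased. Adjustment cannot remove a city effect, and the result is not a clean causal estimate.

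The cost is a revision of the analysis text, a simple rule for missing covariates, and a more modest claim. On the calculation above, baseline adjustment needs no extra patients.

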## Discussion

This study intends to examine the feasibility of a brief intervention; especially motivational interviewing at GP practices carried out within the scope of routine German health checks. It aims to analyze effects on patients’ physical activity, anthropometric data (weight, BMI, waist circumference), arterial blood pressure, activity level, and health-related quality of life. In addition, sociodemographic factors of the patients and GPs are taken into consideration due to their essential impact on individual lifestyle [22, 23]. People with a lower level of education pose a challenge because medical counseling and explanations require more expenditure of time.

The authors believe that this type of brief intervention may not only be employed within the framework of checkups in order to successfully trigger lifestyle changes but that it also has the potential to generally improve the communication between physicians and patients. This is due to its patient-oriented motivating counseling that takes the social situation and individual preferences regarding lifestyle modification into consideration. Because the nurses are deliberately integrated into the setup of the study, it can be anticipated that the cooperation between GPs and their nurses in the supervision of patients over the 6-month study period may have a positive effect on the practice setting. The increased responsibility amongst the staff may potentially strengthen and enhance their position in the practice and thus lead to an improved working atmosphere.

The results may strengthen the role of GPs, including their medical staff, in the prevention of non-communicable diseases and health promotion. Additionally, the study will probably show how exercise recommendations embedded within the framework of routine health checks (Check-Up 35/GOÄ29) can be implemented effectively and efficiently as preventative means for non-communicable diseases. The results of this study will enable us to gather information on the feasibility and the implementation in routine practice. The estimated effect sizes and cluster design effect with the explored prognostic factors will enable the planning of a future cluster-randomized trial.

